### Participants

Participants are children in the fourth grade in public elementary schools in the study area. The inclusion criteria are: [1] attendance at a public school in the Sukhbaatar district; [2] written consent from parents or guardians; and [3] age-appropriate literacy in Mongolian. The exclusion criteria are: [1] comorbidities or contraindications prohibiting participation in an exercise program and [2] enrollment in a special needs program.

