### Primary outcome

The primary outcome of academic achievement will be assessed by the participants’ performance on the examination in 2018, which consists of a mathematics and Mongolian language portion. The participants’ score on the test for May 2017 at the end of third grade will be used as the baseline data.

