### Sample size

Some 2445 children are enrolled in fourth grade at public elementary schools in the Sukhbaatar district of Ulaanbaatar, Mongolia. 2337 children are enrolled in the ten schools that participate in this study. All the eligible children will be recruited.

This study is a longitudinal cluster randomized trial which has three-level cluster units: the school, individual, and measurement time point. Additionally, the number of students at each school differs. To calculate the statistical power, we implemented a simulation study extending the method of a previous study to adjust for unbalanced data. [40] We assumed the standardized difference of the primary outcome to be equal to 0.2, and the dropout rate to be equal to 5%. Since the statistical power of the longitudinal cluster randomized trial depends on the correlation between measurement time points for the same individual, we assumed values of 0.4, 0.5 or 0.6. Bonferroni correction was used to adjust for the multiplicity of statistical testing calculated for each site (Urban/*ger*/mixed residential). Table 1 shows the statistical power and alpha error for each site. We also simulated the disjunctive alpha error and power. In all assumption settings, the disjunctive alpha error is kept nearly equal to 0.05, and the statistical power of the urban site exceeds 0.8. Additionally, under conditions in which the correlation equals 0.6, the statistical power exceeds 0.8 for both sites. The simulation was done 5000 times using the mixed procedure with SAS Software 9.4 (SAS Inc., Cary, NC, USA).

**Table 1 Tab1:** Simulation results of statistical power

Correlation	Disjunctive: 5000 simulations Standardized difference = 0.2					
	Alpha error			Power		
	Total	Urban	*Ger* or mixed residential	Total	Urban	*Ger* or mixed residential
0.4	0.050	0.027	0.024	0.957	0.871	0.642
0.5	0.047	0.023	0.024	0.977	0.920	0.719
0.6	0.047	0.023	0.024	0.992	0.967	0.814

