### Statistical methods

#### Analysis of the primary outcome

The baseline data of the intervention and control groups will be compared. The chi-squared test will be used for binary variables and the t-test will be used for continuous variables. To avoid overestimating the impact of the intervention, an intention-to-treat approach will be adopted to evaluate the impact on the primary and secondary outcomes. In this study, an individual’s data will be analyzed in the originally allocated arm even if the individual moves to a school in another area during study period.

To examine the effect of the intervention while taking the hierarchical structure into consideration, we will use a linear mixed effect model. In this model, the fixed effects are the group (intervention/control), site (Urban/ *ger* or mixed residential), and measurement time point with the following two interaction terms: the interaction between group and measurement time point, and the interaction between the group, measurement time point, and site. The random effects are school and individual. The degrees of freedom will be estimated using Satterthwaite approximation. For the primary analysis, we will compare the participants’ performance on the national year-end examination before and after the intervention using least squares means estimated by the interaction term of the group, measurement time point, and site. The Bonferroni method will be used as a multiplicity adjustment method. A significance level of 0.025 will be set for a two-sided test, and the 95% confidence interval will be calculated.

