#### Subgroup analysis

The effect of the intervention will be further analyzed using four subgroup analyses. The first subgroup analysis will focus on the location of the schools (urban and non-urban areas), the second on gender, and the third on baseline physical fitness performance using the median score on a 20m shuttle run. The fourth subgroup analysis will focus on baseline academic achievement using the total score on the national year-end examination in May 2017 and the median score. The fifth subgroup analysis will be done after excluding participants whose correct rate on the Flanker test is below 80% at either the baseline or endline surveys.

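### The primary contrast takes the change between two different grade-level examinations with no common scale stated, so a difference in spread turns chance baseline gaps between arms into apparent effect

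*Protocol article*

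**What the plan says.** All references are to the Protocol article.

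- **Baseline** (Primary outcome): the "test for May 2017 at the end of third grade will be used as the baseline data".
- **Outcome** (Primary outcome): "performance on the examination in 2018, which consists of a mathematics and Mongolian language portion".
- **Population** (Participants): "Participants are children in the fourth grade in public elementary schools in the study area". The 2018 examination is therefore not the end-of-third-grade paper that supplied the baseline.
- **Model** (Analysis of the primary outcome): a linear mixed model with fixed effects for group, site and time point, plus "the interaction between group and measurement time point, and the interaction between the group, measurement time point, and site". On the random part: "The random effects are school and individual". The 2017 score is an outcome in this model, not a covariate.
- **Effect measure** (same section): results are compared on the year-end "examination before and after the intervention using least squares means estimated by the interaction term of the group, measurement time point, and site", at a two-sided level of 0.025 for each of two sites.
- **Planning** (Sample size): "We assumed the standardized difference of the primary outcome to be equal to 0.2", with a between-time correlation of 0.4, 0.5 or 0.6 and 5% dropout.
- **Allocation**: six urban schools and four *ger* or mixed schools, blocked by number of fourth-grade pupils.

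The article does not say on what scale the scores are analysed, or whether the 2017 and 2018 papers are equated.

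**The concern.** A contrast of before-after change between arms is interpretable when both occasions measure the outcome on the same scale. Here they are papers set for different grades, each with its own difficulty and spread. The time effect removes a difference in average difficulty, because that affects both arms alike. It does not remove a difference in spread.

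Suppose every school and child keeps exactly the same relative standing and the exercise does nothing. If the 2018 paper spreads pupils more widely, any gap between arms at baseline is stretched, and the stretch is read as intervention effect. If the 2018 paper is narrower, the gap shrinks and the sign reverses.

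A gap at baseline is likely because few schools are randomised and they are blocked on size, not on scores. The stated random effects contain no term that lets school means change over time, so the model's standard error does not include this source of variation. What is at stake is the false-positive rate of the sole primary outcome, and the accuracy of the estimate once an imbalance has occurred.

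**Working it through.** **1. Reproduce the plan's own power.** Treat the analysis as a contrast of individual change scores on one scale: difference 0.2, SD of change = √(2(1-ρ)), two-sided level 0.025 (critical value 2.241). The number analysed is 2337 × 0.95 ≈ 2220 children. The article does not give the split by site; 1400 urban and 820 other is assumed. Power = Φ(0.2 / [SD × √(4/N)] - 2.241). At ρ = 0.5 the SD is 1. The urban SE is √(4/1400) = 0.0535 and power is Φ(3.742 - 2.241) = 0.933.

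| ρ | Urban: here / Table 1 | *Ger* or mixed: here / Table 1 | Total: here / Table 1 |
|---|---|---|---|
| 0.4 | 0.880 / 0.871 | 0.645 / 0.642 | 0.957 / 0.957 |
| 0.5 | 0.933 / 0.920 | 0.733 / 0.719 | 0.982 / 0.977 |
| 0.6 | 0.974 / 0.967 | 0.832 / 0.814 | 0.996 / 0.992 |

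All nine agree within 2 percentage points. Table 1 thus corresponds to a change score on a common scale, with no variation between schools in change.

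**2. The artefact.** Let the 2017 SD be 1, the 2018 SD be k, and D the baseline difference between arms. With no treatment effect and unchanged relative standing, the arm difference is D in 2017 and kD in 2018. The contrast is kD - D = (k-1)D.

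**3. Size of a chance gap.** With m schools per arm, SE(D) = √(2·ICC/m), ignoring the small contribution from sampling children within schools. Equal numbers of schools per arm are taken within each stratum.

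- ICC 0.05: √(0.10/3) = 0.183 (3 v 3); √(0.10/2) = 0.224 (2 v 2).
- ICC 0.20: √(0.40/3) = 0.365 (3 v 3); √(0.40/2) = 0.447 (2 v 2).

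**4. Artefact at a one-SE gap, in 2017 SDs.** Both k and ICC are assumptions.

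| k | ICC | Urban | *Ger* or mixed | Share of 0.2 |
|---|---|---|---|---|
| 1.0 | any | 0 | 0 | 0 |
| 1.1 | 0.05 | 0.018 | 0.022 | 9-11% |
| 1.2 | 0.05 | 0.037 | 0.045 | 18-22% |
| 1.25 | 0.05 | 0.046 | 0.056 | 23-28% |
| 1.3 | 0.20 | 0.110 | 0.134 | 55-67% |

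The artefact can go in either direction.

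**5. Type I error.** The stated model was simulated under no effect, 4000 times per setting, with ρ = 0.5 and about 1380 urban and 840 other children. Overall rejection (nominal 0.05):

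| ICC | k = 0.8 | k = 1 | k = 1.1 | k = 1.25 |
|---|---|---|---|---|
| 0.02 | 0.082 | 0.050 | 0.053 | 0.082 |
| 0.05 | 0.141 | 0.046 | 0.066 | 0.130 |
| 0.10 | 0.227 | 0.055 | 0.079 | 0.220 |
| 0.20 | 0.351 | 0.045 | 0.111 | 0.359 |

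**6. Closed-form check at k = 1.25, ICC 0.05.** The variance of change within schools is k² + 1 - 2kρ - (k-1)²·ICC = 1.5625 + 1 - 1.25 - 0.0031 = 1.309.

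- Urban: model SE = √(1.309 × 4/1380) = 0.0616. True SD = √(0.0616² + 0.0456²) = 0.0767, which is 1.245 times larger. Rejection = 2[1 - Φ(2.241/1.245)] = 0.072.
- *Ger* or mixed: model SE = √(1.309 × 4/840) = 0.0790. True SD = √(0.0790² + 0.0559²) = 0.0967, ratio 1.225, rejection 0.067.
- Overall: 1 - (1 - 0.072)(1 - 0.067) = 0.134, against 0.130 simulated.

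**7. After standardising within each examination year,** k = 1 and the artefact is zero for any D. Simulated overall rejection is then 0.045-0.055 for ICC 0 to 0.2.

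**The case against.** The strongest objection is that the article never specifies raw scores. It is silent on the scale, and score derivation is often left to an analysis plan. That is correct. A reader might infer raw marks from the "total score on the national year-end examination in May 2017" in the Subgroup analysis section, but that wording serves only to split children by baseline achievement. What remains is that the contrast itself is fixed in the article, and its validity depends on a common scale that nothing stated there supplies.

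Second, the expected baseline gap is zero under randomisation. This stands, and it rules out a claim of systematic bias. It does not help once a gap has occurred, and it does not restore the type I error.

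Third, the size rests on assumed k and ICC. This also stands. At k = 1.1 with ICC up to 0.05 the inflation is slight. Only variation between schools within strata counts, which may make an ICC of 0.20 too high. The largest figure also shrinks in 2018 units: 0.134/1.3 = 0.103 SD.

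Fourth, standardising removes the artefact fully only if relative standing is otherwise unchanged. True. Differential change between schools is a separate question about the random effects.

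Two further inferences are tempting and are not supported. One is that the weights of mathematics and language are arbitrary. The article does not state the combining rule, which is a detail commonly left elsewhere, and it analyses each subject separately as a secondary outcome. The other is that planning on a standardised 0.2 conflicts with the analysis. Planning in SD units is ordinary and does not oblige the analysis to be in those units.

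**Conclusion.** The concern holds as a conditional weakness of the stated primary contrast. Scores from two different grade-level examinations are treated as repeated measures of one quantity with no stated common scale. If their spreads differ by a factor k, the estimate in each site carries (k-1) times the chance baseline gap, and the model's standard error omits that variation.

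The size is uncertain because k and ICC are not in the document. It ranges from nothing (k = 1) through about a tenth of the 0.2 SD target (k = 1.1, ICC 0.05) to more than half of it in the most adverse combination shown (k = 1.3, ICC 0.20). At ICC 0.05 the simulated overall type I error is 0.066 for k = 1.1 and 0.130 for k = 1.25, against a nominal 0.05. These figures assume unchanged relative standing, a between-time correlation of 0.5 and an assumed split of children by site.

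The change should be made: it protects the sole primary outcome in a ten-school trial at almost no cost.

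**What to change.** Add one sentence to Analysis of the primary outcome. Before the model is fitted, the examination score is standardised separately within each examination year, using the mean and SD of all trial children pooled over both arms and both sites. The stated mixed model is then fitted to the standardised score, and examination points are reported descriptively by arm, site and year.

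No new data are needed and the model is otherwise unchanged. Pooling over arms means that the scaling does not depend on allocation. A true effect of 0.2 SD would inflate the 2018 variance by only about 0.2²/4 = 0.01, which is negligible. The small cost is that the headline result is in SD units and not in examination points. The choice should be fixed before outcome scores are seen, so that the scale cannot be selected with the result in view.

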The intervention will begin in April 2018. Randomized allocation is done in February 2018 and baseline data collection will be done from February to April 2018. The intervention period will be interrupted by summer vacation between the end of June and the beginning of September 2018. The intervention period before summer vacation is the first phase of the intervention and after summer vacation is the second phase of the intervention. Post-intervention data will be collected between November and December 2018. (Fig. 1).

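### The primary model leaves the arms free to differ at a pre-randomisation baseline, so it tests a difference in change scores and may lose some precision that a common-baseline constraint would recover at no cost

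*Protocol article*

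**What the plan says.** All references are to the protocol article.

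- *Primary outcome*: the outcome is the 2018 examination, and "The participants’ score on the test for May 2017 at the end of third grade will be used as the baseline data".
- *Secondary outcomes* (timing paragraph): "Randomized allocation is done in February 2018", nine months after the baseline exam.
- *Analysis of the primary outcome*: "the fixed effects are the group (intervention/control), site (Urban/ *ger* or mixed residential), and measurement time point with the following two interaction terms", namely group by time and group by time by site. "The random effects are school and individual". The comparison is made "before and after the intervention using least squares means estimated by the interaction term of the group, measurement time point, and site", and "A significance level of 0.025 will be set for a two-sided test".
- *Sample size*: "the statistical power of the longitudinal cluster randomized trial depends on the correlation between measurement time points for the same individual", with values of 0.4, 0.5 and 0.6 assumed, a standardised difference of 0.2 and 5% dropout.

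The 2017 score is thus a repeated outcome. It is not a covariate, and nothing ties the arms together at baseline.

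**The concern.** Because the baseline exam precedes randomisation, the arms have equal expected baseline means by design. A model with a free group effect at baseline ignores this. Its group-by-time contrast within a site subtracts the whole observed baseline difference, where an efficient estimator would subtract only the part that predicts the 2018 difference. The estimate stays unbiased, but its variance can be larger than necessary. This matters most in the *ger*/mixed stratum, where there are four schools and the protocol's own power exceeds 0.8 only at a correlation of 0.6.

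The wording adds a smaller problem. A before-and-after comparison of least squares means does not say outright that the tested quantity is the between-arm difference in change within each site.

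**Working it through.** **Inputs from the article.** Standardised difference 0.2; within-child correlation ρ = 0.4, 0.5, 0.6; two-sided alpha 0.025 per site (critical value 2.241); 2337 children, or 2337 × 0.95 ≈ 2220 after dropout; ten schools (6 urban, 4 *ger*/mixed), so about m = 222 children per school.

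**Assumptions, not in the article.** The split of children by stratum (1400/820, chosen to sum to 2220), equal arms, equal school sizes, and the ICC.

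**Step 1: reproduce Table 1.** For a difference in change scores the standard error is √(2(1−ρ) × 4/N). Example, *ger*/mixed at ρ = 0.6: √(0.8 × 4/820) = 0.0625; 0.2/0.0625 − 2.241 ≈ 0.96; power 0.832. Total power is 1 − (1 − urban)(1 − *ger*/mixed).

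| ρ | Table 1: total / urban / *ger*-mixed | Change-score formula |
|---|---|---|
| 0.4 | 0.957 / 0.871 / 0.642 | 0.957 / 0.880 / 0.645 |
| 0.5 | 0.977 / 0.920 / 0.719 | 0.982 / 0.933 / 0.733 |
| 0.6 | 0.992 / 0.967 / 0.814 | 0.996 / 0.974 / 0.832 |

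All nine agree within 2 percentage points. A baseline-adjusted variance, 1−ρ², would need analysed totals of 1526, 1594 and 1694 children at the three correlations. Those totals are inconsistent with each other and far below 2220. Table 1 therefore behaves as a change-score analysis.

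**Step 2: upper limit of the loss.** With no variance between schools, the ratio of constrained to change-score variance is (1−ρ²)/(2(1−ρ)) = (1+ρ)/2, which is 0.70, 0.75 and 0.80. The saving in variance is 30%, 25% and 20%. In the standard error it is 1 − √0.70 = 16%, 13% and 11%.

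**Step 3: allow for schools.** With a stable school effect, the ratio is (1+R)/2, where R is the correlation of school means between the two exams:

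R = (ICC + (ρ−ICC)/m) / (ICC + (1−ICC)/m).

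Example, ICC 0.01 and ρ = 0.5: (0.01 + 0.49/222)/(0.01 + 0.99/222) = 0.01221/0.01446 = 0.844, so the saving is (1 − 0.844)/2 = 7.8%.

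| Assumed ICC | Saving in variance at ρ = 0.4 / 0.5 / 0.6 |
|---|---|
| 0 | 30% / 25% / 20% |
| 0.005 | 14% / 12% / 10% |
| 0.01 | 9% / 8% / 6% |
| 0.05 | 2.5% / 2% / 2% |
| 0.10 | about 1% |

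These figures treat the variance components as known. In simulation with 6 + 4 schools and estimated components, the constrained model had about 0.7 to 0.8 of the change-score variance at ICC 0, about 0.87 to 0.98 at ICC 0.005 to 0.01, and about 1.0 at ICC 0.05 or more.

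**Step 4: departures from a stable school effect on a common scale.** Take ICC 0.05 and ρ = 0.5, with the adjustment coefficient known. If the 2017 standard deviation is k times that of 2018, the ratio is (1−R²)/(1+k²−2kR) with R = 0.959. The saving is 24%, 4%, 2%, 20% and 51% at k = 0.8, 0.9, 1.0, 1.1 and 1.25. With equal standard deviations but school effects correlated 0.8 over time, R falls to about 0.77 and the saving is about 11%. The article gives no information on either quantity.

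**The case against.** The strongest reply is that both analyses are valid and that, in a trial of ten large schools, a stable school effect cancels from the change score. The change-score analysis is then close to efficient. This stands: under the stated model with a material ICC, almost nothing is lost.

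Three stronger readings are tempting, and the documents do not support them.

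- *That the plan throws away 20% to 30% of its precision, and that adjustment would lift the *ger*/mixed stratum past 0.8 power at every assumed correlation.* That is the result for independently randomised children. It needs an ICC of about zero, which the article does not state, and it is a figure for variance, not for the standard error. Such power gains also ignore the few school-level degrees of freedom.
- *That Table 1 shows the plan assumed no clustering.* The sample size section names school as a level. A stable school intercept drops out of the change score at any ICC, so the agreement in Step 1 says nothing about the ICC.
- *That ANCOVA is an equivalent remedy.* With a school intercept, a child-level baseline covariate alone has 1.25 to 1.38 times the change-score variance at ICC 0.01 and 3.2 to 4.4 times at 0.05. Adding the school-mean baseline avoids most of that, but the slope must be estimated from ten schools. In simulation it was 10% to 30% worse than the change score in most settings with ICC 0.01 or more.

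It is also fair to say that the intended between-arm contrast can be recovered from the stated purpose of the model. Naming it is a clarification, not the repair of an undefined test.

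**Conclusion.** The point holds as one of efficiency, not validity. The primary contrast is a difference in change scores with a needlessly free baseline arm difference. The loss is at most 30%, 25% and 20% of variance at correlations of 0.4, 0.5 and 0.6. It is roughly 2% to 13% at an ICC of 0.005 to 0.01 and near zero at 0.05 or more. It could be larger if the exams differ in standard deviation or schools drift. The size cannot be settled from the article, because the ICC, the exam standard deviations and the school-level correlation over time are not given. The change is still worth making: it uses a score already collected before randomisation, and in simulation it was essentially never less precise than the plan.

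This rests on equal arms and school sizes, and on enrolment not depending on the school's allocation, since the constraint applies to the children who enter the analysis.

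**What to change.** Keep the longitudinal linear mixed model with random effects for school and individual and the Satterthwaite degrees of freedom. Constrain the arms to a common baseline mean within each site: drop the group effect at baseline, and keep site, time, site by time, group by time and group by time by site. State that the tested contrast is the between-arm difference at the 2018 exam, separately for the urban and the *ger*/mixed sites, each at 0.025.

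If the exam standard deviations may differ, say whether the covariance structure lets the variance differ by time point. The larger savings in Step 4 depend on that.

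The article carries the primary method over to the continuous secondary outcomes. Their baselines are collected from February to April 2018, with allocation made in February and raters unblinded. Use the constrained form there only where the baseline was measured before allocation was known, or state that assumption.

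Do not replace the model with a child-level or school-mean ANCOVA, and do not revise the power table upwards on this account. The cost is a change of model wording before analysis, with no new data.

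### Single-step Bonferroni for the two site-specific primary tests gives up power that Holm's procedure would recover at the same 0.05 family-wise error

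*Protocol article*

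**What the plan says.** In the Protocol article, under Analysis of the primary outcome, the treatment effect comes from a linear mixed model in which site has two levels. The primary comparison uses "least squares means estimated by the interaction term of the group, measurement time point, and site", which gives one contrast for urban schools and one for ger/mixed schools. On multiplicity the section says "The Bonferroni method will be used as a multiplicity adjustment method" and "A significance level of 0.025 will be set for a two-sided test".

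The Sample size section applies the same rule in the power simulation: "Bonferroni correction was used to adjust for the multiplicity of statistical testing calculated for each site". It reports the outcome as follows: "In all assumption settings, the disjunctive alpha error is kept nearly equal to 0.05, and the statistical power of the urban site exceeds 0.8". Table 1 gives ger/mixed power of 0.642, 0.719 and 0.814 at correlations 0.4, 0.5 and 0.6, so that site passes 0.8 only at 0.6. Neither section mentions a step-down rule or any passing on of alpha.

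**The concern.** With two hypotheses and a family-wise level of 0.05, once one site has been rejected at 0.025 only one hypothesis can still be a true null. It can then be tested at the full 0.05 without raising the family-wise error above 0.05. Single-step Bonferroni never uses this. If urban schools gave p = 0.001 and ger/mixed schools p = 0.03, the plan would call ger/mixed negative, although a rule with the same family-wise guarantee would call it positive.

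The loss falls mainly on the weaker comparison. The ger/mixed stratum has four schools against six urban, and it is the one that Table 1 shows short of 0.8 in two of three settings.

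**Working it through.** **Inputs.** All come from the Protocol article: two tests at two-sided 0.025 (Analysis of the primary outcome); a family-wise target of about 0.05; and Table 1's power by site (Sample size). Critical values are 2.2414 for two-sided 0.025 and 1.9600 for two-sided 0.05. The two sites consist of different schools, so their tests are treated as independent at first.

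**Step 1: confirm the rule behind Table 1.** Two independent tests at 0.025 give a family-wise error of 1 − (1 − 0.025)² = 0.0494; Table 1 shows 0.047 to 0.050. Its per-site alpha errors of 0.023 to 0.027 agree with 0.025, given a Monte Carlo standard error of √(0.025 × 0.975 / 5000) = 0.0022. Disjunctive power should be 1 − (1 − urban)(1 − ger/mixed):

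| Correlation | Calculation | Result | Table 1 total |
|---|---|---|---|
| 0.4 | 1 − 0.129 × 0.358 | 0.954 | 0.957 |
| 0.5 | 1 − 0.080 × 0.281 | 0.978 | 0.977 |
| 0.6 | 1 − 0.033 × 0.186 | 0.994 | 0.992 |

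Table 1 therefore reflects two nearly independent single-step tests at 0.025.

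**Step 2: power of each site at 0.05.** The implied mean of the test statistic is z = 2.2414 + Φ⁻¹(Table 1 power), and power at 0.05 is Φ(z − 1.9600). For ger/mixed at correlation 0.4: z = 2.2414 + 0.3638 = 2.605, so power at 0.05 is Φ(0.645) = 0.741. The other values, computed the same way, are:

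| Correlation | Urban z | Urban at 0.05 | Ger/mixed z | Ger/mixed at 0.05 |
|---|---|---|---|---|
| 0.4 | 3.373 | 0.921 | 2.605 | 0.741 |
| 0.5 | 3.646 | 0.954 | 2.821 | 0.805 |
| 0.6 | 4.080 | 0.983 | 3.134 | 0.880 |

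**Step 3: power under Holm.** Site A is rejected if its p-value is at most 0.025, or if it lies between 0.025 and 0.05 and site B is rejected at 0.025:

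Holm power of A = P_A(0.025) + P_B(0.025) × [P_A(0.05) − P_A(0.025)].

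For ger/mixed at 0.4: 0.642 + 0.871 × (0.741 − 0.642) = 0.728.

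Both sites are rejected with probability P_A(0.025)P_B(0.05) + P_A(0.05)P_B(0.025) − P_A(0.025)P_B(0.025); under Bonferroni it is P_A(0.025)P_B(0.025).

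| Correlation | Ger/mixed, Bonferroni → Holm | Urban, Bonferroni → Holm | Both sites, Bonferroni → Holm |
|---|---|---|---|
| 0.4 | 0.642 → 0.728 | 0.871 → 0.903 | 0.559 → 0.677 |
| 0.5 | 0.719 → 0.799 | 0.920 → 0.945 | 0.661 → 0.766 |
| 0.6 | 0.814 → 0.878 | 0.967 → 0.980 | 0.787 → 0.864 |

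Disjunctive power is identical under the two rules, because Holm's first step is the Bonferroni test.

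**Step 4: error control and dependence.** With 2,000,000 simulated pairs, Holm's family-wise error was 0.0495 when both sites are null. With one null site and the other at a z taken from Step 2 (2.605, 3.37 or 4.08), it was 0.041 to 0.049. Varying the correlation between the two tests from −0.2 to 0.5 left the ger/mixed gain at 6.2 to 8.9 points.

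**Step 5: sensitivity to Table 1.** Table 1's powers can be reproduced within 2 points by a change-score calculation with no between-school variance in change, using 2337 × 0.95 = 2220 children and about 63% to 64% of them in urban schools (an assumption; the split is not given). Adding an assumed between-school variance in change, in squared outcome SD units and with a normal test, changes the ger/mixed gain as follows:

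- variance 0.005: about 6 to 7.5 points;
- variance 0.01: about 4 to 4.6 points;
- variance 0.02: about 2 points, with ger/mixed power below 0.20 under either rule.

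The protocol gives no value for this variance.

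**The case against.** The strongest reply is that nothing here is wrong. Bonferroni with two tests at 0.025 is valid, prespecified and used identically in the simulation and the analysis, and Table 1 shows it controlling the error as intended. Holm leaves the disjunctive power of 0.957, 0.977 and 0.992 untouched. It also lifts no row of Table 1 over 0.8: ger/mixed reaches 0.728 and 0.799 where it was short, and had already passed at correlation 0.6. Both-site power is not a target the protocol sets. The gain shrinks if schools differ in their change over time. Bonferroni also has simple matching simultaneous intervals, which Holm lacks.

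Most of this stands, and it limits the weight of the point: this is an efficiency loss, and the 6 to 9 points hold only on Table 1's assumptions. Two parts do not carry through. Holm is never less powerful, whatever the between-school variance, provided the site p-values are valid, which Bonferroni needs too. And the plan does not use the interval advantage: it pairs 0.025-level tests with 95% intervals, which do not correspond to those tests.

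**Conclusion.** The concern holds as an inexpensive improvement that should be made; the current rule is not invalid. On Table 1's own figures, with a normal approximation and independent sites, Holm adds 8.6, 8.0 and 6.4 points of power in ger/mixed schools and 3.2, 2.5 and 1.3 points in urban schools at correlations 0.4, 0.5 and 0.6, with family-wise error still at most 0.05. It does not change the chance of at least one significant site, and it does not by itself bring ger/mixed power to 0.8 at the two lower correlations. The sizes rest on Table 1 and would be smaller with material between-school variance in change. Holm's dominance over Bonferroni rests on none of these assumptions.

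**What to change.** In Analysis of the primary outcome, replace the Bonferroni sentence and the fixed 0.025 level with wording such as: *The two site-specific contrasts will be tested with Holm's procedure at a two-sided family-wise level of 0.05: the smaller p-value is compared with 0.025 and, if significant, the larger with 0.05.* Report Holm-adjusted p-values, change the matching sentence under Sample size, and restate Table 1 under this rule, adding the both-site power if a claim in both sites is of interest.

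The change has to be fixed before any outcome results are seen. It needs no further schools, children or data. The table can be re-tabulated if the paired p-values from the 5000 runs were kept; otherwise the simulation must be rerun. The one drawback is that simple confidence intervals do not invert the Holm test, so the text should say that the reported 95% intervals are unadjusted and may not agree with the test decision.

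### The two site-specific primary tests run at a two-sided 0.025, but the plan pairs them with an unlabelled 95% confidence interval, where the matching interval is 97.5%

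*Protocol article*

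**What the plan says.** The mixed model described under Analysis of the primary outcome has a two-level site factor, "site (Urban/ *ger* or mixed residential". The primary comparison rests on "least squares means estimated by the interaction term of the group, measurement time point, and site", so there is one before-after group contrast per site. The same section says "The Bonferroni method will be used as a multiplicity adjustment method", and then "A significance level of 0.025 will be set for a two-sided test, and the 95% confidence interval will be calculated".

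The Sample size section gives the reason for the adjustment: "Bonferroni correction was used to adjust for the multiplicity of statistical testing calculated for each site". It also reports that over the two sites together "the disjunctive alpha error is kept nearly equal to 0.05".

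The article does not say that the 95% interval is Bonferroni-adjusted, simultaneous or only descriptive.

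**The concern.** A two-sided test at level a corresponds to the 100(1 - a)% interval: the test rejects exactly when that interval leaves out zero. A test at 0.025 therefore goes with a 97.5% interval, and a 95% interval goes with a test at 0.05. The plan puts 0.025 and 95% in one sentence as though they were a pair.

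The two can then disagree, in one direction only. The 95% interval can exclude zero when the planned test is not significant; the reverse cannot happen. What is at stake is how the primary result is read. A site result that the plan counts as negative would be printed with an interval that looks positive (or harmful), with nothing to tell the reader which of the two governs. The primary outcome is where this matters, because the secondary outcomes are declared exploratory and unadjusted.

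**Working it through.** **Inputs.** Level 0.025 and interval 95%: Analysis of the primary outcome. Two sites: the same section, Allocation and Table 1. Per-site and total alpha and power at a standardized difference of 0.2, from 5000 simulations: Table 1.

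**1. The plan's own figures.** 0.05 / 2 = 0.025. Two independent tests at 0.025 give 1 - 0.975² = 0.0494. Combining the per-site values of Table 1 as 1 - (1 - urban)(1 - ger or mixed):

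| Correlation | Alpha, combined | Alpha, Table 1 | Power, combined | Power, Table 1 |
|---|---|---|---|---|
| 0.4 | 0.0504 | 0.050 | 0.9538 | 0.957 |
| 0.5 | 0.0464 | 0.047 | 0.9775 | 0.977 |
| 0.6 | 0.0464 | 0.047 | 0.9939 | 0.992 |

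The simulation standard error of an alpha near 0.05 is √(0.05 × 0.95 / 5000) = 0.003, and near 0.025 it is 0.002. The per-site alphas of 0.023 to 0.027 and the totals of 0.047 to 0.050 therefore confirm two tests at 0.025 each.

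**2. Width.** Normal multipliers: 1.960 for 95%, 2.241 for 97.5%. 1.960 / 2.241 = 0.874, so the stated interval is 12.6% narrower than the matching one. The other way round, 2.241 / 1.960 = 1.144, so the matching interval is 14.4% wider.

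**3. An example.** An estimate of 2.1 standard errors has p = 0.036, which is not significant at 0.025. Its 95% interval is 2.1 ± 1.960, or 0.14 to 4.06 standard errors, and excludes zero. Its 97.5% interval is 2.1 ± 2.241, or -0.14 to 4.34, and includes zero.

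**4. How often test and interval disagree.** Disagreement means 0.025 < p < 0.05.

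- Under the null: 0.05 - 0.025 = 2.5% per site, and 1 - 0.975² = 4.9% for at least one of the two sites.
- At the planned effect: take the expected test statistic as d = z(power) + 2.241, with power from Table 1. Power at 0.05 is then Φ(d - 1.960), and the difference from the stated power is the probability of disagreement. For the urban site at correlation 0.4: d = 1.131 + 2.241 = 3.37; Φ(1.413) = 0.921; 0.921 - 0.871 = 0.050.

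| Correlation | Urban: power at 0.025 / at 0.05 | Disagreement | Ger or mixed: power at 0.025 / at 0.05 | Disagreement |
|---|---|---|---|---|
| 0.4 | 0.871 / 0.921 | 5.0% | 0.642 / 0.741 | 9.9% |
| 0.5 | 0.920 / 0.954 | 3.4% | 0.719 / 0.805 | 8.6% |
| 0.6 | 0.967 / 0.983 | 1.6% | 0.814 / 0.880 | 6.6% |

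**5. Joint coverage.** With independent sites, two 95% intervals both cover with probability 0.95² = 0.9025. Two 97.5% intervals give 0.975² = 0.951, and at least 0.95 whatever the dependence.

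The school-level simulation itself cannot be rerun, because the article gives neither an intraclass correlation nor the size of each school.

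**The case against.** The strongest case on the other side has three parts.

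*The test carries the error control.* This stands. The decision rule is the 0.025 test, and nothing in the article makes the interval a criterion. A reader might infer that the 95% interval undoes the multiplicity control, since judging both sites by unadjusted 95% intervals would give a familywise error of 1 - 0.95² = 9.75%. The plan does not use that rule. Estimates, p-values, power and sample size are all unaffected.

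*Unadjusted 95% intervals beside adjusted tests are common, and each still covers its own contrast at 95%.* This is true, and the article promises no simultaneous coverage, so the joint 0.90 describes the pair of intervals and breaks no stated target. The practice is clear, however, only when the interval is labelled unadjusted and kept apart from the decision. Here it is unlabelled and shares a sentence with the adjusted level.

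*The wording may mean a Bonferroni-simultaneous 95% interval, with the detail left to the full analysis plan.* That would be 97.5% per site and the conflict would vanish, but the article does not say so. Nor is this missing detail: both numbers are stated, and read as written they do not match.

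A reader might also infer a wider gap by taking degrees of freedom from the number of schools: the 95% interval would be 17.6%, 20.6% or 30.7% narrower at 6, 4 or 2 degrees of freedom. The documents do not support this. The article gives no Satterthwaite values, and its random effects are school and individual only, with no school-by-time term, so both intercepts cancel from a before-after contrast. Table 1 also fits a calculation without a school-level variance. Using 0.2 / √(8(1 - r)/n) against 2.241, with n back-fitted at r = 0.4:

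- Urban, n about 1365: 0.871, 0.927, 0.971, against 0.871, 0.920, 0.967 in Table 1.
- Ger or mixed, n about 814: 0.642, 0.730, 0.829, against 0.642, 0.719, 0.814.

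The two n sum to about 2180, close to 2337 × 0.95 = 2220. Whether the model should have such a term is a separate question.

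**Conclusion.** The mismatch is real and its reach is modest. As written, the interval level does not correspond to the level of the primary test, so a site result with p between 0.025 and 0.05 would carry two conflicting messages. The chance of this is small in the urban site and larger in the ger or mixed site, where Table 1 shows the lower power. The width gap that the documents support is the normal-theory 12.6%.

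These figures rest on a normal approximation, on Table 1 power at a standardized difference of 0.2, and, for the joint figures, on independence of the two sites. The conclusion does not reach the validity of the test or of a 95% interval for a single contrast.

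**What to change.** State that each of the two site-specific primary contrasts will be reported with a 97.5% confidence interval (equivalently, Bonferroni-simultaneous 95% intervals across the two sites). If 95% intervals are shown as well, label them unadjusted and not used for the decision.

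This changes one phrase in the plan and one option in the code. The price is intervals about 14% wider; the test, the sample size and the conduct of the trial stay as they are.
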